## 8. APPENDICES

### Appendix 1

|                                                                   | Study Plan |           |           |   |    |           |
|-------------------------------------------------------------------|------------|-----------|-----------|---|----|-----------|
|                                                                   | Procedures | Screening | Treatment |   |    | Follow-up |
|                                                                   | Visit      | 0         | 1         | 2 | 3  | 3 4       |
|                                                                   | Days       | -2 - 0    | 1         | 7 | 14 | 21±1 28±1 |
| Informed Consent                                                  |            | X         | -         | - | -  | -         |
| Insurance                                                         |            | X         |           |   |    |           |
| PCR for SARS-CoV-2 RNA                                            |            | X         | X         | X | X  | X         |
| ELISA IgM and IgG to SARS-CoV-2                                   |            | X         | -         | - | -  | X         |
| Demographics, Complaints and Medical History, Anthropometric Data |            | X         | X         | - | -  | -         |
| Inclusion and Exclusion Criteria Assessment                       |            | X         | X         | X | X  | X         |
| Physical Examination                                              |            | X         | X         | X | X  | X         |
| Vital Signs Assessment (BP, HR, RR, TEMP)                         |            | -         | X         | X | X  | X         |
| Exclusion Criteria Assessment                                     |            | X         | -         | - | -  | -         |
| Previous Therapy Assessment                                       |            | X         | X         | X | X  | X         |
| Concomitant Therapy Assessment                                    |            | X         | X         | X | X  | X         |

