**NB! Do not use ultrasonic nebulizers for the administration of the combination medication**

## **4. CLINICAL AND LABORATORY ASSESSMENT**

Clinical and laboratory examination of volunteers within 48 hours before the beginning of combination medication usage.

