### **4.1. Complaints Assessment.**

### **4.2. Clinical Examination:**

Physical examination (assessment of the visible mucous membranes of the upper respiratory tract, auscultation and percussion of the lungs, palpation of the lymph nodes, abdominal examination and determination of the size of the spleen and liver, thermometry, BP, HR, RR).

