#### 5.2.2. Adverse events registration and reporting

##### Adverse events (AE)

The protocol requires the registration of all AEs that occur in the patient during and after administration of the medicinal product and until the end of the patient's participation in the trial.

An adverse event is defined as “any untoward medical occurrence in a patient in a clinical investigation who received a medicinal product; the event does not necessarily have to have a causal relationship with this treatment” (National Standard of the Russian Federation GOST R52379-2005 “Good Clinical Practice”).

An AE can be any symptom (including a clinically significant deviation of the laboratory measurement from the reference values), complaint, or disease, the time of occurrence of which does not exclude a causal relationship with the use of the investigational medicinal product, regardless of the existence of such a relationship.

AEs are classified by severity (nonserious or serious AEs), causal relationship with the investigational medicinal product (no/yes; if yes: probable, possible, unlikely, conditional, unclassifiable), and intensity (mild, moderate, severe).

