**Complaints during an examination:** **YES/NO**

If yes, specify, what is present:

Weakness **YES/NO**

Muscular pain **YES/NO**

Headaches **YES/NO**

Dyspnea **YES/NO**

Cough **YES/NO**

Nasal congestion **YES/NO**

Increased temperature **YES/NO**

Sore throat **YES/NO**

Other **YES/NO**

If yes, describe in detail \_\_\_\_\_

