#### Physical examination:

Body temperature \_ \_ °C

Swollen lymph nodes: YES/NO

If yes, underline which nodes are affected: occipital, posterior cervical, parotid, anterior cervical, submandibular, sublingual, supraclavicular and subclavian, axillary, epitrochlear, inguinal, popliteal.

Pharyngeal examination: hyperemia YES/NO

BP sitting \_ \_ / \_ \_ (mm Hg)

HR \_ \_ per min

RR \_ \_ per min

Wheezing in the lungs (dry/wet): YES/NO

If yes, describe nature and location \_\_\_\_\_

Abdominal palpation: soft, painless YES/NO

Liver: aligned with the costal arch: YES/NO

If no, describe in detail \_\_\_\_\_

Spleen: not enlarged YES/NO

If not, describe in detail \_\_\_\_\_

Tested with PCR for SARS-CoV-2 RNA: YES/NO

If yes, indicate the results \_\_\_\_\_

Current therapy: YES/NO

If yes, describe in detail the pharmaceuticals and daily doses \_\_\_\_\_

Assessment of adverse events: YES/NO

If yes, describe in detail the nature of the adverse event \_\_\_\_\_

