#### Specific laboratory diagnostics:

Tested with PCR for SARS-CoV-2 RNA: YES/NO

If yes, indicate the results \_\_\_\_\_

Current therapy: YES/NO

If yes, describe in detail the pharmaceuticals and daily doses \_\_\_\_\_

Assessment of adverse events: YES/NO

If yes, describe in detail the nature of the adverse event \_\_\_\_\_

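### Symptoms are asked item by item only at Visit 0 and by a single open adverse-event item afterwards, so airway symptoms are elicited unevenly before and after the first dose

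*Protocol*

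**What the plan says.** The Study Plan in Appendix 1 places complaints in a combined row, "Demographics, Complaints and Medical History, Anthropometric Data". It is marked at screening and Day 1 and dashed at Day 7, Day 14 and in the follow-up column (Days 21 and 28).

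Section 4 opens with "Clinical and laboratory examination of volunteers within 48 hours before the beginning of combination medication usage" and lists "4.1. Complaints Assessment" under it.

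In the individual record form, Visit 0 has a block headed "Complaints during an examination" with nine YES/NO items: weakness, muscular pain, headaches, dyspnea, cough, nasal congestion, increased temperature, sore throat and other. The forms for Days 1, 7, 14 and 21 do not contain it. They have "Assessment of adverse events: YES/NO", followed by "If yes, describe in detail the nature of the adverse event".

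Safety reporting is broad. Section 5.2.2 states that "An AE can be any symptom", and its definition also covers complaints. Section 5.2.1 has adverse events assessed at every visit and also during and after each administration. The subsection on registering adverse events includes those that the volunteer describes subjectively.

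The product description states, for potassium chloride and for the inosine compound alike, that no data exist on inhaled use. Section 2.4 plans to infer from the absence of a given type of event that its rate is below 5%.

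**The concern.** Cough, dyspnea and sore throat are the symptoms one would look for with an inhaled product that has no inhalation data, and section 1.2 also lists them among the first signs of COVID-19. The plan asks about each by name before any product is inhaled. Afterwards it relies on a general question about adverse events.

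A requirement to register every event settles what must be written down once it is known. It does not ensure that each symptom is asked about. If mild symptoms come up less readily under the open question, recorded rates are too low, and the error favours the product. Section 2.4 makes this matter more, because reading zero recorded events as a low true rate depends on near-complete capture.

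**Working it through.** **Schedule and forms side by side**

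| Visit | Complaints in Appendix 1 | Itemised list on form | AE item on form |
|---|---|---|---|
| Visit 0 | marked | yes, nine items | yes |
| Day 1 | marked | no | yes |
| Day 7 | dash | no | yes |
| Day 14 | dash | no | yes |
| Day 21 | dash (follow-up column) | no | yes |
| Day 28 | dash (follow-up column) | form not in the text available | not known |

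Two things follow. Plan and form disagree at Day 1. And no visit after Day 1 is scheduled for complaints.

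Wheezing, temperature, respiratory rate and pharyngeal hyperemia are recorded at Visit 0 and again on Days 1, 7, 14 and 21, so these can be compared with baseline. Cough, dyspnea, sore throat and nasal congestion as reported by the volunteer cannot be compared item by item.

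Dosing four times daily for 14 days gives 4 × 14 = 56 administrations against three treatment-period visits (Days 1, 7, 14). None of the visit forms shown has a per-administration field in which the assessments promised in section 5.2.1 would be entered.

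**The plan's own safety figure (section 2.4)**

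Inputs: 100 subjects, event probability 5%, stated chance of at least one event about 95%.

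- 1 − 0.95^100 = 99.4%, so the stated figure is not reproduced.
- 1 − 0.97^100 = 95.2%, so 95% corresponds to a probability of 3%.

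That mismatch is a separate matter. Here it means that the 5% statement has some slack if every event is recorded.

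**Effect of incomplete capture (illustration)**

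Let s be the share of affected volunteers whose symptom is recorded. The protocol gives no value, so s is assumed throughout.

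With 0 of 96 recorded, the one-sided 95% upper bound on the recorded rate is 1 − 0.05^(1/96) = 3.07%. The bound on the true rate is 3.07% / s:

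- s = 1: 3.1%
- s = 0.7: 4.4%
- s = 0.5: 6.1%
- it reaches 5% at s = 3.07 / 5 = 0.61

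With 100 subjects the bound at full capture is 1 − 0.05^(1/100) = 2.95%, and it reaches 5% at s = 2.95 / 5 = 0.59.

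For a true rate of 5% in 100 subjects, the chance of recording at least one event is 1 − (1 − 0.05s)^100:

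- s = 1: 99.4%
- s = 0.9: 99.0%
- s = 0.7: 97.2%
- s = 0.5: 92.0%
- s = 0.3: 77.9%

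**The case against.** The best defence is that symptoms on treatment are already covered. Adverse events include any symptom or complaint, are assessed at every visit and around every administration, and include what the volunteer describes. Each form shown has an adverse-event item, and several objective signs are repeated. This stands, and it rules out some stronger readings that a reader might draw:

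- *Complaints are never assessed on treatment.* Appendix 1 marks them on Day 1, within the treatment period. What is missing is the block on the Day 1 form. The wording in section 4, "within 48 hours before the beginning of combination medication usage", does not settle it either: the same heading covers the physical examination and RT-PCR, which Appendix 1 repeats later.
- *No comparison with baseline is possible.* The repeated signs can be compared, and a later cough recorded as an adverse event can be checked against the Visit 0 list. Only the like-for-like symptom items are lost.
- *Symptoms will be under-counted.* This is a plausible risk of open questioning, but the protocol neither shows nor quantifies it.
- *The product has never been inhaled.* The text says only that there are no data on inhaled administration.
- *Baseline complaints that vanish will be reported as improvement.* Section 6 plans no analysis of change in complaints.

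The adverse-event registration form, an appendix to the record, is not in the text available and may prompt for more. Even so, it is completed once an event has been identified, so it is unlikely to replace asking about each symptom.

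The slack in section 2.4 also counts for the defence: at 50% capture, the chance of recording at least one event of true rate 5% in 100 subjects is still 92.0%.

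**Conclusion.** The point holds as a weakness in data collection, not as a failure to monitor safety. Itemised symptom questioning appears on the Visit 0 form and on none of the forms shown for Days 1, 7, 14 and 21. Appendix 1 schedules complaints at none of the four visits after Day 1, and the Day 1 form contradicts the Day 1 tick.

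The consequence is uneven elicitation before and after the first dose, no item-by-item comparison for reported airway symptoms, and a possible loss of mild events. There is no concurrent group questioned in the same way against which to read the result.

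The effect on the zero-event inference is conditional. The 5% reading survives if at least about 61% of affected volunteers are recorded (96 subjects), and fails below that. Only the 3.07% bound is derived; every capture rate is an assumption. No conclusion is drawn about the Day 28 form. The change is worth making because it is cheap and removes the uncertainty, not because a bias has been demonstrated.

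**What to change.** 1. In Appendix 1, split complaints from demographics, history and anthropometric data, and mark complaints at every visit: screening and Days 1, 7, 14, 21 and 28.
2. Reconcile the Day 1 form with the Day 1 tick by adding the complaints block.
3. Copy the Visit 0 block, wording unchanged, into every later visit form, including Day 28 if it is not already there.
4. Have any item that is new or worse than at Visit 0 recorded under the existing rules in section 5.2.2. No new adverse-event rule is needed.

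The cost is an edit to the schedule and forms that reuses an existing block, and by my estimate about a minute per visit at visits already planned. The downside is that more mild events will be recorded, so tolerability will look slightly less favourable.

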## **Instruction for Use of Combination Medication**

### **1. Preparation of Combination Medication**

A combination of the medication is prepared per daily inhalation dose by mixing the following medication in the indicated amount *ex tempore*:

3% solution of inosine glycyl-cysteinyl-disodium glutamate - 4.0 ml;

4% potassium chloride solution - 1.0 ml.

One milliliter of a solution of a combination medication contains the following active substances:

Inosine glycyl-cysteinyl-disodium glutamate - 24.0 mg

Potassium chloride - 8.0 mg

### **2. Dosage and Administration of the Combination Medication**

The combination medication is administered daily in the daytime 4 times a day with an interval of at least 4 hours.

The combination medication should be used within 24 hours after preparation.

A single inhalation dose of the combination medication is 1.25 ml.

A single dose of medication of the combination is as follows:

Inosine glycyl-cysteinyl-disodium glutamate – 30.0 mg

Potassium chloride – 10.0 mg

A daily dose of medication of the combination is as follows:

Inosine glycyl-cysteinyl-disodium glutamate – 120.0 mg

Potassium chloride – 40.0 mg

The combination medication is administered by inhalation using a nebulizer equipped with a mouthpiece. The nebulizer is connected to the compressor to create the required air flow (5-8 l/min). The combination medication should be inhaled through the mouthpiece of the nebulizer in a calm and regular manner.

The recommended duration of combined medicinal product use is 14 days.

### **3. Other Recommendations**

The nebulizer will be regularly cleaned following the manufacturer's instructions. The cup of the nebulizer will be cleaned after each use. The cup of the nebulizer and mouthpiece or mask will be washed with warm water and mild detergent (following the manufacturer's instructions). The nebulizer will be thoroughly rinsed and dried by connecting the cup to the compressor or air inlet valve.

### **4. Special indications**

Do not use ultrasonic nebulizers for the administration of the combination medication.

Protocol: MIBVD-19 Low-Intervention Study of the Aerosol Use of Combination Medication as Pre-Exposure Prophylaxis for the Novel Coronavirus Infection COVID-19.

## Visit 0 (Screening)

### Study day -2-0

Date \_ \_ . \_ \_ . \_ \_ \_ \_ \_

Height \_ \_ \_ (cm)

Weight \_ \_ (kg)

#### Bad habits:

Smoking: **YES/NO**

If yes, specify how many cigarettes per day \_\_\_\_\_

Allergies: **YES/NO**

If yes, specify, to what and how it is manifested \_\_\_\_\_

Use of alcohol: **YES/NO**

If yes, specify what kind of alcohol and the weekly amount (ml) \_\_\_\_\_

#### Medical history:

Cardiovascular diseases: **YES/NO**

If yes, specify \_\_\_\_\_

Treatment for cardiovascular diseases: **YES/NO**

If yes, specify which medications and in what dose are taken daily \_\_\_\_\_

Pulmonary diseases: **YES/NO**

If yes, specify \_\_\_\_\_

Treatment for pulmonary diseases: **YES/NO**

If yes, specify which medications and in what dose are they taken daily \_\_\_\_\_

Gastrointestinal diseases: **YES/NO**

If yes, specify \_\_\_\_\_

Treatment for gastrointestinal diseases: **YES/NO**

If yes, specify which medications and in what dose are they taken daily \_\_\_\_\_

Musculoskeletal system diseases: **YES/NO**

If yes, specify \_\_\_\_\_

Treatment for musculoskeletal system diseases: **YES/NO**

If yes, specify which medications and in what dose are they taken daily \_\_\_\_\_

Diabetes: **YES/NO**

Treatment for diabetes: **YES/NO**

If yes, specify which medications and in what dose are they taken daily \_\_\_\_\_

Acute respiratory viral infections or influenza in the last 3 months: **YES/NO**

**Complaints during an examination:** **YES/NO**

If yes, specify, what is present:

Weakness **YES/NO**

Muscular pain **YES/NO**

Headaches **YES/NO**

Dyspnea **YES/NO**

Cough **YES/NO**

Nasal congestion **YES/NO**

Increased temperature **YES/NO**

Sore throat **YES/NO**

Other **YES/NO**

If yes, describe in detail \_\_\_\_\_

**Physical examination:**

**Body temperature** \_\_\_\_ °C

**Swollen lymph nodes:** **YES/NO**

If yes, underline which nodes are affected: occipital, posterior cervical, parotid, anterior cervical, submandibular, sublingual, supraclavicular and subclavian, axillary, epitrochlear, inguinal, popliteal.

**Pharyngeal examination:** hyperemia **YES/NO**

**BP sitting** \_\_\_\_/\_\_\_\_(mm Hg)

**HR** \_\_\_\_per min

**RR** \_\_\_\_ per min

**Wheezing in the lungs (dry/wet):** **YES/NO**

If yes, describe the nature and location

**Abdominal palpation:** soft, painless **YES/NO**

**Liver:** aligned with the costal arch: **YES/NO**

If no, describe in detail \_\_\_\_\_

**Spleen:** not enlarged **YES/NO**

If not, describe in detail \_\_\_\_\_

**Specific laboratory diagnostics:**

**Tested with PCR for SARS-CoV-2 RNA:** **YES/NO**

If yes, indicate the results \_\_\_\_\_

**Current therapy:** **YES/NO**

If yes, describe in detail the pharmaceuticals and daily doses \_\_\_\_\_

**Assessment of adverse events:** **YES/NO**

If yes, describe in detail the nature of the adverse event \_\_\_\_\_

**Assessment of inclusion/exclusion criteria**

**Inclusion criteria**

Healthy volunteers aged between 18 and 80 years: **YES/NO**

Informed consent form signed by a healthy volunteer: **YES/NO**

Ability of a volunteer to cooperate adequately (the volunteer can understand the information provided about the study and is willing to comply with the requirements of the study protocol): **YES/NO**

**Exclusion criteria**

Healthy volunteers cannot be included in the trial if they meet at least one of the following criteria.

Criteria related to the underlying disease:

Detection of SARS-CoV-2 virus RNA by polymerase chain reaction (PCR) for COVID-19 in biomaterial samples and positive reactivity of enzyme-linked immunosorbent assay (ELISA) IgM and ELISA IgG to the virus in a healthy volunteer: **YES/NO**

Criteria related to the combination medication, previous therapy and concomitant therapy: **YES/NO**

Hypersensitivity or individual intolerance to the components of the combination medication products according to the medical history: **YES/NO**

Criteria related to the concomitant pathology:

According to the medical history and physical examination: **YES/NO**

Any diseases or conditions that, in opinion of the investigator, make it difficult to interpret the results of treatment or may limit the participation of a healthy volunteer in the study: **YES/NO**

According to screening laboratory tests:

Related to the compliance of healthy volunteers in the study: **YES/NO**

Any other diseases or conditions that, in the opinion of the investigator, would make it difficult to interpret the results of treatment or may limit the participation of a healthy volunteer in the study: **YES/NO**

Healthy volunteers who, in the opinion of the investigator, are obviously or likely unable to understand and evaluate the information regarding this study within the process of signing the informed consent form, in particular, regarding the expected risks and possible discomfort: **YES/NO**

The inability or unwillingness of a healthy volunteer to follow the rules for carrying out the study and participating in a clinical trial: **YES/NO**

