### **2.6. Exclusion Criteria**

Healthy volunteers cannot be included in the trial if they meet at least one of the following criteria.

2.6.1. Criteria related to the disease:

Detection of SARS-CoV-2 virus RNA by polymerase chain reaction (PCR) in biomaterial samples and/or positive enzyme-linked immunosorbent assay ELISA IgM and ELISA IgG to the virus in a healthy volunteer;

2.6.2. Criteria related to the combination medication, previous therapy and concomitant therapy:

Hypersensitivity or individual intolerance to the components of the combination therapy according to the medical history.

2.6.3. Criteria related to the concomitant pathology:

According to the medical history and physical examination:

- any diseases or conditions that, in opinion of the investigator, would make it difficult to interpret the results of treatment or may limit the participation of a healthy volunteer in the study.

According to screening laboratory tests:

- related to the compliance of healthy volunteers in the study;
- any diseases or conditions that, in opinion of the investigator, would make it difficult to interpret the results of treatment or may limit the participation of healthy volunteers in the study;

Healthy volunteers who, in the opinion of the investigator, are obviously or likely unable to understand and evaluate the information regarding this study within the process of signing the informed consent form, in particular regarding the expected risks and possible discomfort.

The inability or unwillingness of a healthy volunteer to follow the rules for carrying out the study and participating in a clinical trial.

2.7. **Early Discontinuation Criteria**

2.7.1. A healthy volunteer will be excluded from the study if SARS-CoV-2 virus RNA is detected in biomaterial samples by a polymerase chain reaction (PCR) for COVID-19 or if enzyme-linked immunosorbent assay (ELISA) IgM and ELISA IgG results are positive.

2.7.2. A healthy volunteer may withdraw their consent to participate in the study at any time and without giving reasons. The investigator may also decide on early discontinuation of the participation of a healthy volunteer in the study at any time if the patient's condition requires it.

2.7.3. Main reasons for early discontinuation of participation of a healthy volunteer in the study:

Individual intolerance to the combination medication or any of its components;

Failure to meet the inclusion and exclusion criteria;

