**Based on the assessment of the inclusion/exclusion criteria, the healthy volunteer may be admitted to the study: YES/NO**

### **Assessment of exclusion criteria**

A healthy volunteer will be excluded from the study if SARS-CoV-2 virus RNA is detected in biomaterial samples by a polymerase chain reaction (PCR) for COVID-19 or if there is positive reactivity to enzyme-linked immunosorbent assay (ELISA) IgM and ELISA IgG: **YES/NO**

A healthy volunteer may withdraw their consent to participate in the study at any time and without giving reasons. The investigator may also decide on early discontinuation of the participation of a healthy volunteer in the study at any time if the patient's condition requires it: **YES/NO**

Main reasons for early discontinuation of participation of a healthy volunteer in the study: **YES/NO**

Individual intolerance to the combination medication products or any of its components: **YES/NO**

Failure to meet the inclusion/exclusion criteria: **YES/NO**

Refusal of a healthy volunteer from participation in the study/withdrawal of informed consent by a healthy volunteer: **YES/NO**

Development of AEs that prevent further prophylactic therapy with the combination medication products: **YES/NO**

Emergence of a serious adverse event in a healthy volunteer: **YES/NO**

The emergence of exclusion criteria in the course of the study: **YES/NO**

Any condition of a healthy volunteer that requires, in the opinion of the investigator, the withdrawal of the patient from the study: **YES/NO**

Discontinuation of the trial by the research center, investigator, or regulatory authority: **YES/NO**

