#### Assessment of exclusion criteria

A healthy volunteer will be excluded from the study if SARS-CoV-2 virus RNA is detected in biomaterial samples by a polymerase chain reaction (PCR) for COVID-19 or if there is positive reactivity to enzyme-linked immunosorbent assay (ELISA) IgM and/or IgG: **YES/NO**.

A healthy volunteer may withdraw their consent to participate in the study at any time and without giving reasons. The investigator may also decide on early discontinuation of the participation of a healthy volunteer in the study at any time if the patient's condition requires it: **YES/NO**

Main reasons for early discontinuation of the participation of a healthy volunteer in the study: **YES/NO**

Individual intolerance to the combination medication or any of its components: **YES/NO**

Failure to meet the inclusion/exclusion criteria: **YES/NO**

Refusal of a healthy volunteer to participate in the study or withdrawal of informed consent by a healthy volunteer: **YES/NO**

Development of AEs that would prevent further prophylactic therapy with the combination medication: **YES/NO**

Emergence of a serious adverse event in a healthy volunteer: **YES/NO**

The emergence of exclusion criteria in the course of the study: **YES/NO**

Any condition of a healthy volunteer that requires, in the opinion of the investigator, the withdrawal of the patient from the study: **YES/NO**

Discontinuation of the trial by the research center, investigator, or regulatory authority: **YES/NO**

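### The SARS-CoV-2 entry rule differs between section 2.6.1 and the record forms used to decide admission, and no version excludes an IgG-only volunteer

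*Protocol*

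**What the plan says.** The rule on PCR and antibody results appears in four forms in the protocol.

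- **Entry, section 2.6.1:** RNA detected "in biomaterial samples and/or positive enzyme-linked immunosorbent assay ELISA IgM and ELISA IgG to the virus".
- **Entry, record form, Visits 0 and 1 (Exclusion criteria):** RNA detected "in biomaterial samples and positive reactivity of enzyme-linked immunosorbent assay (ELISA) IgM and ELISA IgG to the virus", as a single YES/NO item. On both forms the line that admits the volunteer follows from these boxes.
- **Discontinuation, section 2.7.1 and record form, Visits 1 and 2:** RNA detected, or IgM and IgG positive. The Visit 1 form reads "or if there is positive reactivity to enzyme-linked immunosorbent assay (ELISA) IgM and ELISA IgG".
- **Discontinuation, record form, Visits 3 and 4:** RNA detected, or "if there is positive reactivity to enzyme-linked immunosorbent assay (ELISA) IgM and/or IgG".

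The Study Plan in Appendix 1 has a row for "ELISA IgM and IgG to SARS-CoV-2", marked at screening and in follow-up, with a dash on Days 1, 7 and 14. PCR is marked at screening and at each later visit, including Day 1. The Visit 0 form has a result field for PCR ("Tested with PCR for SARS-CoV-2 RNA") but none for ELISA.

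Section 2.2 defines the efficacy endpoint as RT-PCR positivity within 28 days. The protocol states no rule for positivity already present at baseline. Section 6 takes the data of all enrolled volunteers into the efficacy analysis. Section 2.4 sets an expected rate of 3% or less against a reference rate of 11.1%, with 96 subjects.

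**The concern.** The text that governs eligibility and the form that records it give opposite answers for the same test results. Both also leave open the case of past infection shown by IgG alone.

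Two kinds of wrong entrant matter, and they act in opposite directions. A volunteer already PCR-positive at entry can become a case that the product could not have prevented, which raises the observed rate. A volunteer with IgG from past infection may be less susceptible, which lowers the observed rate for a reason unrelated to the product. In a randomised trial both would tend to balance between arms. Here one observed proportion is judged against an outside figure, so nothing balances them. At 3% the plan expects only 96 × 0.03 = 2.9 cases, so a single misclassified person is a large part of the count.

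**Working it through.** **Step 1: the two entry texts side by side, read literally.**

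| Screening result | Section 2.6.1 | Visit 0 and 1 form box |
|---|---|---|
| PCR+, IgM−, IgG− | excluded | not excluded |
| PCR+, IgM+, IgG+ | excluded | excluded |
| PCR−, IgM+, IgG+ | excluded | not excluded |
| PCR−, IgM−, IgG+ | not excluded | not excluded |
| PCR−, IgM+, IgG− | not excluded | not excluded |

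The first and third rows are contradictions. The last two are gaps common to both texts.

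**Step 2: reproduce the plan's own sample size.** Inputs from section 2.4: p0 = 0.111, p1 = 0.03, alpha 0.05. The stated beta error of 0.85 works only as power 0.85. One-sample normal approximation, two-sided alpha:

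n = [(1.960 × √(0.111 × 0.889) + 1.036 × √(0.03 × 0.97)) / (0.111 − 0.03)]²

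= [(1.960 × 0.3141 + 1.036 × 0.1706) / 0.081]² = 95.7, rounded up to 96.

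The figure reproduces and is not in dispute. The one-sided version gives 73.3, so two-sided alpha fits 96 better, although the protocol does not state sidedness.

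**Step 3: a success limit (assumption).** The protocol states none. I took the largest c with P(X ≤ c | 96, 0.111) at or below the tail probability.

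- Two-sided 0.05 (lower tail 0.025): c = 4, with P(X ≤ 4 | 96, 0.111) = 0.0145 and power P(X ≤ 4 | 96, 0.03) = 0.838.
- One-sided 0.05: c = 5, with false-success chance 0.0376 and power 0.931.

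**Step 4: k baseline PCR-positive entrants counted as cases (k is an assumption).** Power = P(X ≤ c − k | 96 − k, 0.03).

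| k | c = 4 | c = 5 |
|---|---|---|
| 0 | 0.838 | 0.931 |
| 1 | 0.681 | 0.843 |
| 2 | 0.462 | 0.688 |
| 3 | 0.228 | 0.469 |

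**Step 5: m immune entrants and no drug effect (m is an assumption, as is a reference cohort without such persons).** False-success chance = P(X ≤ c | 96 − m, 0.111). Expected rate = 0.111 × (96 − m)/96.

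| Share immune (m) | Expected rate | c = 4 | c = 5 |
|---|---|---|---|
| 0% (0) | 11.1% | 0.0145 | 0.038 |
| 10% (10) | 9.9% | 0.032 | 0.074 |
| 20% (19) | 8.9% | 0.061 | 0.131 |
| 30% (29) | 7.8% | 0.122 | 0.232 |

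**The case against.** A reader might infer that the protocol as a whole admits PCR-positive volunteers. It does not. Section 2.6.1 excludes on PCR alone, and only the record form says otherwise. The Visit 1 form also carries a discontinuation line under which detected RNA is enough on its own, and both entry forms have a general item for conditions that would hamper interpretation. An investigator who follows 2.6.1 will not enrol a known PCR-positive. This part of the objection stands. The Visit 1 line, however, comes after the Visit 0 admission decision, and section 6 keeps enrolled volunteers in the efficacy analysis. Nothing in the protocol takes such a person out of the primary count.

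A reader might also infer from the Visit 3 form that an IgG-only volunteer admitted at entry would be removed on Day 14. The Study Plan schedules no ELISA on that day, and the form has a result field for PCR only, so no result is planned that would trigger it. The wordings differ, but that consequence does not follow.

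The sizes are open to fair challenge. The success limit and the numbers of wrong entrants are mine, and the one-sided limit softens the power loss. The immune scenario also requires that the cohort behind 11.1% did not itself contain previously infected people. The protocol does not say. If that cohort held a similar share, the comparison would not be tilted in this way.

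An analysis plan, not at hand, could define how baseline positives are counted. It could not settle who is eligible, which belongs to the protocol and its form.

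**Conclusion.** The inconsistency is real and rests on the text alone. Section 2.6.1 and the entry forms disagree on a PCR-positive, antibody-negative volunteer, and every entry version lets a PCR-negative, IgG-only volunteer through. The first problem is confined to the form and is partly guarded by 2.6.1 and the Visit 1 check. No explicit rule covers the second.

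The effect on the primary rate is a risk, not an established distortion. Under the assumptions above, one baseline-positive entrant counted as a case costs between 0.09 (0.93 to 0.84, one-sided limit) and 0.16 (0.84 to 0.68, two-sided limit) of power. An immune share of 10 to 30% raises the false-success chance from 1.5% to about 3 to 12% under the two-sided limit. The two errors act in opposite directions. The documents give no basis for a net effect, nor for assuming that they cancel.

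**What to change.** - Use one entry rule, worded identically in section 2.6.1 and on the Visit 0 and Visit 1 forms: a positive PCR, a positive IgM or a positive IgG at screening each makes the volunteer ineligible. Give each its own box, and add an ELISA result field to the Visit 0 form.
- State that a volunteer whose screening or Day 1 sample proves PCR-positive is reported as infected at baseline and not as an incident case in the primary rate. Show the all-enrolled count required by section 6 alongside.
- Reconcile the discontinuation wordings in 2.7.1 and on the Visit 1 to Visit 4 forms with each other and with the ELISA schedule in Appendix 1. Which rule should apply there is for the sponsor and investigators to decide.

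Both tests are already scheduled at screening, so the cost is small form changes and a few more screen failures. The sample size of 96 is unaffected.
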